### Eligibility and recruitment

The target group for the intervention is legal representatives, both professional and volunteer. Additionally, data will be assessed from all people with dementia who are represented by one of the participating legal representatives at least for 2 weeks within the 6-month follow-up (hereby referred to as *persons concerned*).

Legal representatives who represent at least one person with dementia (assessed by the legal representative and / or medical diagnosis) are eligible for inclusion. Exclusion criteria are former participation in the PRODECIDE education program (either the whole program or a single module).

Recruitment will be performed consecutively in cooperation with institutions that offer training for professional or voluntary representatives. Institution cooperation includes recruitment and conducting the education program. Appointments for the education program will be made, and invitations will be published, using the e-mail lists, websites, calendar of events, flyers, etc., of the cooperating institutions. The invitation covers information about both the education program (e.g., target group, content, place and time) and the study (e.g., randomized allocation, offers for the control group).

Potential participants will register at the study center (by phone, e-mail or fax). After screening for eligibility (by phone), the legal representatives will receive information leaflets, the consent form and forms for baseline assessment (by mail or e-mail).

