### Outcomes

The primary outcome measure is *knowledge*, which is operationalized as an understanding of decision-making processes in healthcare affairs and in setting realistic expectations regarding probabilities of benefits and harms of PEG, PR and AP to people with dementia.

Secondary outcome measures are: 1) legal representatives have obtained sufficient knowledge (using a cut-off of 70% correct answers in the knowledge test); 2) legal representatives have obtained sustainable knowledge, which is measured 6 months after intervention; 3) percentage of persons concerned affected by PEG, FEM or AP during follow up of 6 months; and 4) result of the first decision after intervention regarding PEG, PR and AP for the persons concerned including time to first decision.

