Additionally, the number of PEG, PR and AP interventions in the persons concerned will be assessed (Table 1). The legal representatives will perform the assessment as at T0, filling out the documentation sheets and forwarding any copies of routine documentation. New diagnoses since baseline, the presence of PEG, the number and types of PR, medication data and decisions made about one of these interventions will be documented.

All persons concerned who are represented by one of the participating legal representatives at least for 2 weeks within the 6-month follow-up are eligible. If a person concerned who was assessed at T0 is no longer represented by the participant prior to end of follow-up, a documentation sheet will be filled out. The time of and reason for dropout, as well as the presence of PEG, number and types of PR and medication data at the time of dropout, will be documented. New persons concerned during the study period will be assessed at the time of inclusion and at T3. At the time of inclusion, a documentation sheet will be filled out, including time of inclusion, age range, gender, any diagnoses additional to dementia, the presence of PEG, number and types of PR and medication data.

Participants will receive the knowledge test and documentation sheets by mail or, if requested, by email. Participants in the CG have to submit the documents before subsequently beginning the education program (they may hand them over in person on the first training day).

Participants who had not made all three decisions regarding PEG, PR or AP for a person concerned at T2 will be additionally contacted by phone and asked again if they had made a decision since T2. Results of the first decision of each intervention will be recorded as in T2.

To reach a high compliance rate until T3, participants will receive stamped, addressed envelopes for returning outcome assessments by mail. Submission of all documents to the study center will be also possible by email or fax. If required, participants will be reminded by phone, and any of their questions about data assessment will be answered.

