### Data analysis

Data will be entered into a SPSS database and double-checked by student assistants blinded to the group allocation. Simple plausibility checks will be done in the study center before the final statistical analysis by the statistician. Analysis of all quantitative data will use the intention-to-treat principle. Missing values in primary and secondary outcomes will be imputed using simple methods. A dropout analysis comparing baseline parameters between the study population and early dropouts (before T2) will be performed.

All statistical tests are two-sided using a significance level of 5%. Baseline parameters are described by frequency tables, means, standard deviations or quartiles.

The primary outcome is the percentage of correct answers for the knowledge test at T1. Assuming approximate normal distribution, the expected values from the IG and CG will be compared with adjustment for stratified randomization by professionals and volunteers using bifactorial analysis of variance (linear model). Distribution assumptions will be investigated by graphical methods. Furthermore, interactions between intervention and professional status will be included in a secondary model. Different effects depending on the professional status will be discussed.

The secondary outcome of sufficient knowledge (binary) at T1 will be compared between IG and CG using bivariate logistic regression, including IG/CG and professional status as independent variables. Additionally interactions between intervention and professional status will be investigated in a second model.

The sustainability of knowledge will be investigated at T3. The time course of the knowledge between T1 and T3 will be analyzed by fitting a linear mixed model: the dependent variable is knowledge (% of correct answers), and the independent variables are IG/CG, time (T1, T3), interaction between intervention and time, professional status and interaction between intervention and professional status. To adjust for repeated measurements of the legal representatives, random effects are included (covariance pattern model with covariance structure compound symmetry).

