Further secondary outcomes are the numbers of persons concerned and the percentage of these persons affected by PEG, FEM or AP (separately) per legal representative at T3. Mean values ± standard deviations will be described for IG and CG at T3 as well as at T0. Linear models will be fitted including IG/CG and initial values at T0 as independent variables.

Finally, the results of the first decision about PEG, FEM or AP by the legal representative after T0 (e.g., after training for IG, or after randomization for CG) will be assessed. Initially, the duration from T0 to the first decision will be described for IG and CG by Kaplan-Meier curves. In case of no decision, durations are censored at the end of observation after 6 months or at dropout. Kaplan-Meier curves between both groups will be compared by the log rank test, as long as there are no clear deviations from the proportional hazard assumption in the graphics. Four categories of decisions will be described by frequency tables.

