### Sample size

No information was available for the primary outcome from previous studies. The assessment instrument was pretested with a before-after design to roughly estimate the expected intervention effect in the primary outcome of knowledge (given as a percentage of correct answers). The knowledge test was revised after three courses with a total of 18 legal representatives. Afterwards, two pilot courses with 16 participants were used to estimate the effect size of the intervention. Fifteen datasets before intervention, and 12 after intervention, were included in the analysis.

A common standard deviation of σ = 0.17 can be assumed in IG and CG. A mean difference of 0.085 between IG and CG can be detected by a power of 90% by the two-sided t-test, using a significance level of 5% based on a sample size of 86 per group (172 overall). Including a maximum dropout rate of 20%, an overall sample size of 216 is planned. The pilot study estimated a larger effect (0.38). Because of the low sample size, and considering a possible bias in the pilot study, the planned sample size is higher than theoretically necessary. It corresponds to a medium effect of 0.5*σ, as suggested by Cohen.

With six to ten participants per training session, the education program will be offered approximately 24 times (12 times per group).

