## Discussion

In this RCT, we will evaluate the efficacy of the PRODECIDE education program in the context of training for legal representatives.

The PRODECIDE study has several strengths. Legal representatives will be allocated to the intervention or to the control group using a computer-generated randomization scheme. An independent person not involved in either the study or data collection will perform the allocation. Data entry will be performed blinded. Various approaches will be taken to reduce missing data and dropouts. These strategies were adapted from previous RCTs with very low attrition rates [20, 60, 61]. For analysis, the intention to treat principle will be used.

The study limitations include the fact that, due to the nature of the intervention, neither participants nor researchers conducting the education program and data collection will be blinded. Likewise, it is not possible to safeguard either the inclusion of all eligible persons with dementia or the correct documentation of PEG, PR and AP for all persons concerned. Only the legal representatives will perform the assessment for eligibility, and they will give the data of the persons concerned to the study center under a pseudonym. We assume that the error ratio will be comparable in IG and CG. Nevertheless, it is possible that enhanced knowledge in the IG leads to a more correct documentation and to a bias of results. Data collection will be verified by using medical and nursing records if possible. Finally, legal representatives are well connected, for instance through office partnerships or supervision sessions, such that “contamination” from the intervention to the control group by sharing educational materials is possible. However, as the training is both hands-on and in-depth, we do not expect that the CG has an improved knowledge solely on the basis of written educational materials.

At the end of this study, information about the efficacy of the PRODECIDE education program, the usability of e-learning modules and processes that interfere with or promote a successful implementation into the regular training curricula for legal representatives will be available.

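### The T3 percentages for PEG, restraints and antipsychotics count persons who enter after randomisation on unblinded representatives' judgement, so this secondary comparison can be biased in either direction

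*Protocol article*

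**What the plan says.** All places are in the protocol article.

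- **Randomisation and blinding:** allocation follows consent and baseline data, so the T0 list of persons concerned is complete before the arm is known. Representatives cannot be blinded.
- **Eligibility and recruitment:** data are taken on all people with dementia "represented by one of the participating legal representatives at least for 2 weeks within the 6-month follow-up". This population is not limited to the T0 list.
- **Data collection:** "New persons concerned during the study period will be assessed at the time of inclusion and at T3". Time of inclusion and status at inclusion are recorded. If a person on the T0 list leaves, status at that time is recorded too.
- **Discussion:** "Only the legal representatives will perform the assessment for eligibility". The authors concede that complete inclusion and correct documentation cannot be ensured and that better knowledge in the intervention group could bias documentation. They assume similar error in both arms.
- **Outcomes:** the secondary outcome is the "percentage of persons concerned affected by PEG, FEM or AP during follow up of 6 months".
- **Data analysis:** the outcomes are the number of persons concerned and "the percentage of these persons affected by PEG, FEM or AP (separately) per legal representative at T3", described by arm at T0 and T3. The linear model contains group and the T0 value. No analysis restricted to persons listed at T0 is described.

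**The concern.** The T0 list is protected by randomisation because it precedes allocation. The T3 denominator is not, because it adds persons identified later by someone who knows the allocation and, in the intervention group, has had the training. If the arms add different numbers of persons, or different kinds of persons, the T3 percentage moves although nobody's care has changed. The T0 percentage cannot absorb this, since the later entrants are not in it.

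At stake is the trial's stated further objective, a clinically relevant reduction of PEG, restraints and antipsychotics. The wording also differs on whether the outcome covers the six months or the T3 time point. That difference bears on whether persons who left before T3 count.

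**Working it through.** **1. The plan's own figure.** The only calculated size in the article is for the primary outcome, knowledge at T1: "A common standard deviation of σ = 0.17 can be assumed in IG and CG" and "A mean difference of 0.085 between IG and CG can be detected by a power of 90% by the two-sided t-test". The normal approximation is n = 2 × (1.960 + 1.282)² × (0.17/0.085)² = 84.1, so 85 per group. The exact t-test needs 85.03, so 86, with power 0.903. Dropout: 86/0.8 = 107.5, so 108 per group and 216 overall. The stated figures are reproduced and are not touched by this point. No figure is given for the percentages of persons affected.

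**2. Inputs for the shift.**
- From the Background section: prevalence p of 5% (PEG), 12.5% (restraints) and almost 30% (antipsychotics, taken as 30%). These are for nursing home residents, so using them for persons concerned is an assumption.
- Assumed, because the article gives no values: f, the share of intervention-group persons at T3 who are excess entrants (0.1 to 0.3), and r, prevalence among entrants relative to the T0 list (0 to 1.5).

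**3. Formula.** With care unchanged, an arm's pooled T3 percentage is (1 − f)p + f·r·p, so its shift is −f·p·(1 − r). Between arms the spurious difference is p × [f_IG(r_IG − 1) − f_CG(r_CG − 1)]. It is zero if entry and entrant prevalence are the same in both arms, or if entrants resemble the T0 list in both arms (r = 1). Otherwise it is in general not zero.

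**4. Results, excess entry in the intervention group only (percentage points).**

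| Outcome | f = 0.1, r = 0.5 | f = 0.2, r = 0.5 | f = 0.2, r = 0 | f = 0.3, r = 0 |
|---|---|---|---|---|
| Antipsychotics, 30% | −1.5 | −3.0 | −6.0 | −9.0 |
| Restraints, 12.5% | −0.6 | −1.25 | −2.5 | −3.75 |
| PEG, 5% | −0.25 | −0.5 | −1.0 | −1.5 |

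With r = 1 every entry is 0. With r = 1.5 the antipsychotic shift is +1.5 (f = 0.1) to +4.5 (f = 0.3).

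**5. Does T0 adjustment help?** The planned linear model (T3 percentage on group and T0 percentage) was simulated under further assumptions: 86 representatives per arm, k persons each at T0, 90% of treated persons still treated at T3, the same prevalence across representatives, 2,000 runs per setting and no effect on care.

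- No excess entry (f = 0): rejection 4.3 to 5.6%, against a nominal 5%.
- Antipsychotics, k = 5: 11% (f = 0.1, r = 0.5), 35% (f = 0.2, r = 0.5) and 92% (f = 0.2, r = 0).
- Antipsychotics, f = 0.2, r = 0.5: 15% at k = 2 and 66% at k = 10.
- Restraints and PEG, k = 5, f = 0.2, r = 0.5: about 15% and 10%.
- r = 1: 4.5 to 5.9%.

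The average simulated shift is a little smaller than in step 4 (−2.6 rather than −3.0 points for antipsychotics at k = 5, f = 0.2, r = 0.5), because percentages are averaged per representative. The T0 covariate does not remove it.

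**The case against.** Much of the case for leaving the plan alone is fair.

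- **Clients are assigned by a court** (Background), so a representative does not choose truly new clients. This stands. The discretion lies in deciding which clients count as having dementia. The wording that lets the representative's own assessment suffice sits in the inclusion criterion for representatives. Only the Discussion puts the eligibility of persons concerned in their hands.
- **Numbers of persons concerned are a planned outcome by arm.** Differential listing may therefore show. This is a real safeguard against missing the problem, but it does not correct the percentages, and a total count mixes entrants with leavers.
- **The Discussion discloses the weakness.** It does so in part. It does not name entry after randomisation, and equal error is assumed, not tested.
- **An open cohort is a legitimate choice.** A caseload percentage per representative is a coherent outcome, the T0 percentage is a sensible covariate for the randomised unit, and newly assigned persons are also affected by trained representatives' decisions. This stands, and is why the open-cohort result should be kept.
- **The mismatch in wording is minor.** Table 1 and Data analysis both point to T3. How status at leaving is used may be settled in an analysis plan that is not shown.

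A reader might infer that the percentages will fall in the intervention group and flatter the programme. The article does not support a direction. It describes no teaching on recognising dementia, and it expects that better knowledge could improve documentation, which might raise recorded use. A reader might also infer that randomisation no longer protects this comparison at all. It still protects persons listed at T0. The threat comes through later entrants.

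**Conclusion.** The point holds as a possible bias of unknown size and either sign in one set of secondary outcomes. Persons can enter the T3 percentage after allocation on the sole judgement of unblinded representatives, and neither T0 adjustment nor the planned count of persons corrects a difference in entry.

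For antipsychotics the spurious shift is −1.5 to −9 points if excess entrants are 10 to 30% of intervention-group persons at T3 and have 0 to 50% of a 30% prevalence. It is zero at equal prevalence and +1.5 to +4.5 points at one and a half times the prevalence. These are illustrations. Caseload, entry rate and entrant prevalence are all assumed, and the base rate is a nursing-home figure. The extreme case, extra persons in one arm only and none of them treated, should not be read as an estimate. The primary outcome and the sample size of 216 are unaffected.

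**What to change.** 1. Base the main between-arm comparison of PEG, restraints and antipsychotics on persons documented at T0 before randomisation, using status at T3 or, for those who left, the status already recorded when representation ended.
2. Report the open-cohort percentage alongside, with the number of later entrants and their status at inclusion, by arm.
3. Use one definition in Outcomes and Data analysis: either over the six months or at T3, saying how persons who leave are counted.

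The cost is a change of analysis wording. Data collection already provides time of inclusion, status at inclusion and status at leaving. The main comparison would rest on fewer persons and make no claim about newly assigned ones. It would also leave in place the separate limitation that unblinded representatives report the T3 status themselves.

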### Randomization and blinding

After retrieval of written informed consent and baseline data, participants will be allocated to the intervention group or to the control group, stratified by professionals and volunteers (Fig. 1). To ensure a close balance of entities in each group, randomization will be performed by randomly selected block sizes of four and six. The randomization list will be computer generated by a scientist who is not involved in either the intervention or data collection. An independent person will also perform the allocation. As safeguards, no other person will have access to the list, and the list will be sent by e-mail only in an encrypted format.

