**Fig. 1 Fig1:**
[figure not shown]
Study Flow

Due to the nature of the intervention, blinding of the participating legal representatives and the researchers conducting the education program is not possible. Independent persons and an external biometrician, blinded to the group allocation, will perform data entry and data analysis, respectively.

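### The secondary PEG/PR/AP comparison counts persons registered after randomisation by the unblinded representative, and adjustment for the T0 percentage cannot remove a shift if that registration differs by arm

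*Protocol article*

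**What the plan says.** **Who counts.** Under Data collection in the protocol article, "All persons concerned who are represented by one of the participating legal representatives at least for 2 weeks within the 6-month follow-up are eligible". Being on the T0 list is not required: "New persons concerned during the study period will be assessed at the time of inclusion and at T3". For entrants, the time of inclusion and PEG, PR and medication status at inclusion are recorded.

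**Who decides.** The Discussion states: "Only the legal representatives will perform the assessment for eligibility". The section on randomisation and blinding says that "blinding of the participating legal representatives and the researchers conducting the education program is not possible".

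**When.** "After retrieval of written informed consent and baseline data, participants will be allocated to the intervention group or to the control group". The T0 list is therefore complete before the arm is known, and every later entry is made after it is known.

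**Those who leave.** An exit sheet with PEG, PR and medication status is planned "If a person concerned who was assessed at T0 is no longer represented by the participant prior to end of follow-up".

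**Analysis.** Under Data analysis, the outcome is the percentage of persons affected per representative at T3, separately for each intervention. Means and standard deviations are described by arm at T0 and T3, and "Linear models will be fitted including IG/CG and initial values at T0 as independent variables". The article does not limit the T3 percentage to persons on the T0 list, and it does not analyse later entrants separately.

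**The concern.** Representatives are randomised, but the T3 percentage is computed over people whose membership is partly settled afterwards. Randomisation balances the T0 lists on average. It gives no such guarantee for people added later by someone who knows the allocation and, in the intervention group (IG), has had a 10-hour course on decisions for people with dementia.

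The T0 percentage in the model does not help here. It describes only the people listed before allocation and carries no information on how many were added later or how they differ.

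The Objectives section names a clinically relevant reduction of PEG, PR and AP as a further objective, and this comparison is one of the analyses that address it. A difference in registration between the arms could imitate a reduction or hide one.

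**Working it through.** **The plan's own figure.** The only sample size is for the knowledge test. The standardised difference is 0.085/0.17 = 0.5. A two-sided 5% t-test with 90% power needs 85.03 per group, rounded up to 86. Then 86/0.8 = 107.5, rounded up to 108 per group, gives 216. The figure reproduces and is not in dispute. No power is stated for the PEG/PR/AP percentage; 86 per arm is used below only as a plausible number of analysed representatives.

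**Inputs.** Prevalence p in T0 persons is taken from the Background section: AP about 30%, PR 12.5%, PEG 5%, all for nursing home residents. Two quantities are not in the documents and are assumed:
- s, the share of T3 persons in the IG who are extra post-randomisation entrants
- q, the prevalence among those entrants

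**Formula.** With no treatment effect and extra entry in the IG only, the T3 percentage in the IG is (1 − s)p + sq, and in the control group (CG) it is p. The difference is s(q − p). With entry in both arms it is s_IG(q_IG − p) − s_CG(q_CG − p), which is zero when entry is the same in number and kind.

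**Illustration.** Add 20% extra persons with 10% AP use to a list at 30%: (0.30 + 0.20 × 0.10)/1.20 = 0.32/1.20 = 26.7%. Equivalently, s = 0.20/1.20 = 0.167 and s(q − p) = 0.167 × (−0.20) = −3.3 points.

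**Range for AP (p = 30%), in percentage points:**

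| s | q = 0 | q = 15% | q = 30% | q = 45% |
|---|---|---|---|---|
| 10% | −3.0 | −1.5 | 0 | +1.5 |
| 20% | −6.0 | −3.0 | 0 | +3.0 |
| 30% | −9.0 | −4.5 | 0 | +4.5 |

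With q = 0, s from 10% to 30% gives −1.25 to −3.75 points for PR and −0.5 to −1.5 points for PEG.

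**Does T0 adjustment remove it?** The stated linear model (group plus T0 value) was simulated for AP with no treatment effect. Assumptions: 86 representatives per arm, 5 T0 persons each, intraclass correlation 0.1, the same background change in both arms, extra entry in the IG only, 1,000 trials per scenario.

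| s | q | Estimated difference (points) | False-positive rate |
|---|---|---|---|
| 10% | 0 | −2.6 | 25% |
| 20% | 0 | −5.2 | 81% |
| 30% | 0 | −8.3 | 99% |
| 10% | 15% | −1.2 | 9% |
| 20% | 15% | −2.8 | 28% |
| 30% | 15% | −4.1 | 56% |
| 10–30% | 30% | about 0 | about 5% |

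The estimates are slightly smaller than s(q − p) because the outcome is an average of per-representative percentages, with random numbers of entrants. The q = 0 rows are extremes: no entrant uses AP and the CG gains nobody.

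A second simulation used less extreme assumptions: half the representatives with 5 persons and half with 1, 15% new persons in both arms, and 20% extra in the IG at 10% AP use. It gave −2.1 points and a false-positive rate of 12%. With the extra persons at 60% AP use it gave +3.3 points and 20%.

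**Restriction to T0 persons.** The estimate was about 0 and the false-positive rate 3–6% in every scenario of the first simulation. In the second it was 4–6%, with no loss of precision (standard error 0.028 against 0.029).

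**The case against.** **The mechanism is not shown.** Representatives are appointed by court, so most entrants are probably new appointments, which training is unlikely to influence. The course covers decision-making and the evidence on PEG, PR and AP; nothing says that it teaches recognition of dementia. This stands. A reader might infer that training will change who is registered and so bias the result. The article does not establish that.

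**The rule on dementia status.** A reader might take "assessed by the legal representative and / or medical diagnosis" as the rule for adding persons during follow-up. It stands in the criterion for the representative's own entry to the trial. The support for representative-only judgement of persons concerned comes from the Discussion.

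**The limitation is partly disclosed.** The Discussion says that complete inclusion cannot be guaranteed and assumes comparable error by arm. It then concedes that greater knowledge in the IG could bias documentation, and plans checks against records where possible. That is fair disclosure. However, records can confirm the status of registered persons; they do not show who was left unregistered.

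**Much is already collected.** The number of persons per representative is to be described by arm at T0 and T3, so a gross imbalance would be visible. Someone who joins and leaves early has a recorded status at inclusion, and imputation is planned for missing secondary outcomes; it would be wrong to say that nothing is known about such a person. Late joiners counting the same as others is dilution, not bias in itself.

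**An open cohort can be the intended target.** Including new clients measures the effect on a representative's whole practice. That is a legitimate question and a reason to keep the analysis as supportive. It does not make it safe as the main comparison when membership is judged after allocation without blinding.

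**Details may lie in an SAP.** A T0-only set could be defined there. The point here is what the article does state: the open eligibility rule and the T3 percentage with T0 adjustment.

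**Conclusion.** The concern holds in conditional form. The article leaves a route by which arm-dependent registration after randomisation shifts the PEG/PR/AP difference by s(q − p), and the planned T0 adjustment does not close it. Two conditions must both be met: the rate or type of later registration differs by arm, and entrants' prevalence differs from that of T0 persons. If either fails, the shift is zero.

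Size and direction are unknown, because s and q are assumptions throughout; the 26.7% against 30% is an illustration, not a forecast. The stronger conclusion, that this outcome is biased or that a reduction would be spurious, is not supported.

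The point concerns a secondary outcome. The primary knowledge comparison at T1 is untouched, and the first-decision results also bear on the further objective. The change is worth making because it is cheap and removes this route.

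**What to change.** In the Data analysis section:

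1. Base the main PEG/PR/AP comparison on the persons on the T0 list. Compute the T0 and T3 percentages on the same persons, using the recorded exit status for those no longer represented at T3.
2. Keep the open-cohort T3 percentage as a supportive analysis.
3. Report by arm the number of post-randomisation entrants and their PEG, PR and AP status at inclusion.

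No new data are needed. Every eligible representative has at least one person with dementia at entry, so a T0 percentage should exist for each, and T0, exit and T3 status are already to be collected for listed persons.

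The cost is analysis wording, with two limits. Decisions for newly represented persons move to the supportive analysis, so the main result speaks to existing clients only. The change also does not cure differential documentation of T0 persons by unblinded representatives, which remains a limitation.
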